**Fig. 1 Fig1:**
[figure not shown]
CONSORT Flow Diagram of Detailed Progress of Subjects in the Trial

### Ethical approval

Ethical approval will be obtained from the appropriate institutional ethics committee prior to the initiation of the trial. Ethical approval will be obtained from the Ministry of National Health Services, Regulation and Coordination (Pak Secretariat, Islamabad), M/o National Health Services Regulation and Coordination (District Health Office-ICT), National Bioethics Committee (NBC) and Yale University.

## Eligibility, sampling, recruitment, enrollment, and consent procedures

### Eligibility

#### Inclusion criteria

Women of reproductive age (between 18 and 45 years) are either pregnant or have a child under 3 years; report a positive response to item 9 of the Urdu Patient Health Questionnaire (PHQ-9); can speak Urdu fluently; have access to a mobile phone; are connected to primary health care services; and intend to live in the study area for at least 6 months.

#### Exclusion criteria

Women requiring immediate inpatient care for medical or psychiatric conditions, no access to a mobile phone, and unable to speak and understand Urdu.

#### Sampling procedures

The trial aims to recruit a total of 50 participants at risk of suicide and allocated into two equal groups: an intervention arm (*n* = 25) and an EUC arm (*n* = 25) based on their cluster randomization. This sample size is consistent with recommended guidelines for pilot randomized-controlled trials [30] and is sufficient for the primary goal of estimating key feasibility parameters, including recruitment rates, retention, and preliminary effect sizes, to inform the design of a future definitive trial, rather than for testing statistical significance. Participants will be identified by screening for suicidal ideation (in partnership with the local government health system) across six VCs. Based on extant literature and preliminary formative data, which estimate a 5–8% prevalence rate, we will screen approximately 800 women to ensure adequate recruitment across this range. The target analytic sample for all subsequent 3- and 6-month follow-up assessments will remain 50 participants, with robust retention strategies employed to minimize attrition. We will also aim to recruit 12 peer mothers to be trained as delivery agents for the KPZ intervention.

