### Implementation outcomes

Adoption, reach, fidelity, feasibility, acceptability, and appropriateness will be assessed using a combination of quantitative indicators (e.g., participation, completion, number of KPZ sessions delivered) and validated implementation scales (AIM, IAM, FIM), alongside qualitative interviews, focus group discussions, and longitudinal reflections with peer mothers, supervisors, LHWs, and medical officers. To understand how well the KPZ intervention was received, a combination of quantitative tools and qualitative methods will be used to explore its relevance, appropriateness, and overall acceptability from the perspectives of those implementing and engaging with it.

Three brief standardized scales, the Feasibility of Intervention Measure (FIM), Acceptability of Intervention Measure (AIM), and Intervention Appropriateness Measure (IAM), will be used to assess how implementing agents perceived the intervention [41]. Each scale contains four items rated on a 5-point Likert scale (from “completely disagree” to “completely agree”). FIM will measure how practical and easy the intervention was to deliver. AIM will assess whether the implementers found the intervention appealing and welcomed the approach. IAM will assess how well the intervention seemed to fit the context and needs of the population. Together, these tools provide a quick yet meaningful snapshot of implementers’ views on the intervention’s usability and relevance.

Finally, peer mother knowledge, attitudes, and confidence to implement KPZ will be assessed using the 30-item Knowledge, Attitudes, and Confidence (KAC) scale (Table 3) [42].

**Table 3 Tab3:** A priori progression criteria for a definitive full-scale trial

	Go-proceed with RCT	Amend-proceed with changes	Stop-do not proceed unless
1.Feasibility of participant recruitment Can 50 trial participants (Assuming each village cluster can recruit 8 participants) be recruited to take part in the study?	If at least 38 trial participants Could be recruited to take part in the study	If < 38 participants are recruited To take part in the study	If < 20 participants are recruited To take part in the study

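### About 800 screens give an expected 40 positive women at the plan's own lower prevalence of 5%, so they do not cover a target of 50 across 5–8%

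*Protocol article*

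**What the plan says.** Sampling procedures gives the target: "The trial aims to recruit a total of 50 participants at risk of suicide", split equally between arms. The same paragraph takes a prevalence from earlier work and draws the screening number from it: "which estimate a 5–8% prevalence rate, we will screen approximately 800 women to ensure adequate recruitment across this range". It names no other recruitment target and no rate of eligibility or consent among women who screen positive.

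The inclusion criteria require that a woman "report a positive response to item 9 of the Urdu Patient Health Questionnaire (PHQ-9") and also cover age, maternal status, Urdu, mobile phone access, a link to primary care and intended residence. The exclusion criteria remove women who need immediate inpatient care. Table 2 makes the percentage of eligible women who consent a feasibility outcome.

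Table 3, criterion 1, asks whether 50 participants can be recruited. It sets the Go grade as: "If at least 38 trial participants Could be recruited to take part in the study". Below 38 is Amend and below 20 is Stop.

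**The concern.** The sentence claims that one screening number is enough for every prevalence between 5% and 8%. A number that covers a range has to be worked out at the least favourable end, here 5%. Eight hundred looks instead like a figure from the middle of the range.

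The consequence lies in interpretation, since the trial is not powered for a test. Recruitment is the first progression criterion and the recruitment rate is one of the parameters the pilot exists to estimate. If about 800 women are screened, prevalence is near 5% and recruitment falls short, the cause could be too few screens or too few willing and eligible women. These call for different changes to the definitive trial, and the recruited count alone does not tell them apart.

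**Working it through.** **Inputs from the article.** Target 50; prevalence 5% to 8%; screens about 800 (all Sampling procedures). Go mark 38 (Table 3). **Assumption.** Uptake, meaning the share of positive women who are eligible and enrol, is not given; I show 70% to 100%.

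**Step 1: where 800 comes out right.** Prevalence needed = 50 / 800 = 6.25%, with full uptake. The midpoint of 6.5% needs 50 / 0.065 = 769.2, so 770 screens. The stated figure therefore fits the middle of the range.

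**Step 2: the whole range, full uptake.** Expected positives = 800 × prevalence. Screens for an expected 50 = 50 / prevalence, rounded up. The last column is the exact binomial probability of at least 50 positives among 800.

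| Prevalence | Positives from 800 | Screens for 50 | P(at least 50) |
|---|---|---|---|
| 5% | 40 | 1,000 | 0.065 |
| 6% | 48 | 834 | 0.40 |
| 6.25% | 50 | 800 | 0.52 |
| 6.5% | 52 | 770 | 0.63 |
| 7% | 56 | 715 | 0.82 |
| 8% | 64 | 625 | 0.97 |

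At 5% the shortfall is 50 − 40 = 10 women, or 10 / 50 = 20% of target, and 1,000 − 800 = 200 screens. The probabilities treat women as independent. Clustering by village would widen the spread but leave the expected counts unchanged.

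**Step 3: allowing for uptake (assumed).** Recruits = 800 × prevalence × uptake. Screens for 50 at the lower bound = 50 / (0.05 × uptake).

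| Uptake | Recruits from 800, at 5% to 8% | Screens for 50 at 5% | P(at least 38 recruits) at 5%, 800 screens |
|---|---|---|---|
| 100% | 40 to 64 | 1,000 | 0.65 |
| 90% | 36 to 57.6 | 1,112 | 0.39 |
| 80% | 32 to 51.2 | 1,250 | 0.16 |
| 70% | 28 to 44.8 | 1,429 | 0.04 |

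**Step 4: the Go mark.** At 5%, reaching 38 from an expected 40 positives needs 38 / 40 = 95% of them to enrol.

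**The case against.** The strongest reply is that the article says *approximately* 800, plans 1.5 years of recruitment (Study design) and nowhere says that screening stops at 800. That stands. A reader might infer that the pilot is bound to be graded Amend at 5% prevalence because of this number. The text does not support that: Table 3 grades the number recruited, whatever the number screened, and even 40 expected positives exceed 38. An Amend grade would need low prevalence, losses at a rate the article does not give, and screening that in fact ends near 800. Still, the word *approximately* cannot absorb a gap of 200 screens.

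A second reply is that adequate recruitment means 38, not 50. Sampling procedures does not say so, and Table 3 also asks about 50. On that reading the margin would still be thin (step 4).

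A third is that uptake may be close to full. The informed consent section places consent before screening, so some refusals may come before a woman counts as screened, although the recruitment section also describes consent at enrolment. Lady Health Workers are trained to approach distressed women, so the screened group may be enriched. Both points make the 80% row uncertain. Neither touches the 40 against 50, which already assumes no losses and uses the plan's own prevalence.

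A reader might also see errors in three nearby figures. They are not errors:

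- Six clusters at 8 each is 48, but 50 / 6 = 8.3, so this is rounding in a parenthetical assumption ("Assuming each village cluster can recruit 8 participants").
- A follow-up target of 50 ("The target analytic sample for all subsequent 3- and 6-month follow-up assessments will remain 50 participants") does not contradict a Go mark of 70% retention: one is an aim, the other a floor.
- Multiplying the two floors, 38 × 0.70 = 26.6, does not give the number analysed. The quantitative analysis section specifies intention-to-treat with mixed models that use all available data, so a woman lost at 6 months still contributes.

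**Conclusion.** The point holds in a limited form. The claim that about 800 screens suffice across 5–8% is wrong from 5% up to 6.25%. At 5% the expected number of positives is 40, which is 20% below target with no losses at all. This rests only on the article's own figures. The recruit counts at 70% to 90% uptake rest on assumed rates and show direction and scale only.

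Severity is moderate to minor. The trial is an unpowered pilot with exploratory analyses, and a shortfall would itself be a feasibility result. What makes the correction worthwhile is that recruitment feeds a go/amend/stop decision.

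**What to change.** Choose one of two restatements in Sampling procedures.

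1. **Raise the number.** State at least 1,000 screens for the lower bound, divided by a declared uptake: about 1,110 at 90%, 1,250 at 80%. These figures give an expected 50, not a guaranteed 50; at 6.25% with 800 screens, where the expectation is also 50, the chance of reaching it is only 0.52. First check that the six village clusters can supply that many eligible women. The randomization section puts each at about 2,400–3,600 people, so 14,400–21,600 in all, but the article does not give the number of eligible women among them. Cost: 1,000 − 800 = 200 to 1,250 − 800 = 450 more brief screens, and no rise in the enrolment target.
2. **Keep 800.** State the expected yield of 40–64 positives (about 32–51 recruits if 80% enrol, labelled as an assumption) and remove the claim that it covers the whole range. Cost: wording only.

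In both cases, report the number screened and the observed prevalence when grading progression criterion 1, so that a shortfall from too few screens is not read as infeasible recruitment. The trial is described as ongoing; if screening has already closed, the second option and this reporting step are still available.

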### Recruitment procedures

#### Screening

Screening procedures were co-developed with the CAB, LHWs, and the local government health system. Women of reproductive age identified by LHWs within their catchment areas across Shah Allah Ditta and Sihala UCs will be approached for screening by LHWs who then introduce trained members of the research team. Screening will assess recent suicidal ideation and eligibility for study participation. Women who meet eligibility criteria will be invited to participate in the trial.

### Recruitment

During the co-design phase of the KPZ intervention, LHWs were oriented to the study objectives and trained to sensitively approach women experiencing suicidal distress and their families within their catchment areas. Women who report suicidal ideation within the past 2 weeks and meet eligibility criteria will be recruited into the study following informed consent obtained by the research team. Enrolled participants will be followed up at 3- and 6-months post-recruitment. Participants in the intervention arm will receive the peer-delivered intervention. Participants in both study arms will be referred to the Medical Officer (MO) at the respective primary healthcare facility, who is trained in the WHO mhGAP including identifying and managing common mental conditions and suicide. If imminent suicide risk is identified, the research team will negotiate with the participant and her family to refer her to specialized psychiatric care at the nearest hospital. Participants allocated to the control arm will receive EUC, with the same referral and safety procedures applied in cases of active suicidal ideation. Written informed consent will be obtained from all participants in both study arms prior to enrollment.

### Informed consent procedure

Careful attention to informed consent and other study safety procedures was co-designed with the CAB to optimize salience, understanding, and collective safety. Trained research assistants will obtain written informed consent from all participants prior to any study procedures. The consent form will be read aloud to participants, and, with the participant’s permission, one or more trusted household members may be present during the consent process to support understanding and decision-making. Informed consent will be obtained prior to screening and baseline interviews, with consent reaffirmed verbally at the 3- and 6-month follow-up assessments. All interviews will be conducted at locations preferred by participants, in their homes, the LHW Health House, or another preferred location.

Participants will be informed that all personal information will be kept confidential, that study data will be anonymized and stored securely in locked cabinets and password-protected systems, and that data will be used solely for research purposes. Participants will also be informed of the specific circumstances under which confidentiality may be breached to protect their safety or the safety of others, as well as the procedures that will be followed in such cases. As part of the consent process, participants will be asked to identify an emergency contact in the event that a confidentiality breach is required. Where appropriate and with participant consent, family members may be engaged as part of safety planning to support participant well-being. Scripts for engaging and negotiating with family members were designed by the CAB.

Further, potential peer mothers will be identified by LHWs within their respective VC/UCs. An orientation meeting will be conducted with eligible candidates at their respective primary healthcare facilities, during which the goals of the KPZ intervention and the responsibilities of the peer mother role will be explained in detail. Women who express interest and meet eligibility criteria will be invited to participate and written informed consent will be obtained prior to their recruitment. Formal engagement of peer mothers will be completed through written agreements outlining their roles, responsibilities, and ethical obligations within the KPZ intervention.

### Refusal to consent

Participation in the study will be entirely voluntary. Participants will be able to withdraw their consent from any part of the study at any time, including the intervention and/or follow-up, without needing to provide a reason.

## Assessments

### Baseline assessment

All baseline assessments will be conducted by trained members of the research team who are blinded to participants’ allocation status. Baseline data will include sociodemographic characteristics, including age, marital status, reproductive history (including previous pregnancies and miscarriages), educational attainment, and employment status.

Baseline assessments will also measure the severity of suicidal ideation, depression, and anxiety; perceived social support; suicide-related cognitions; exposure to intimate partner violence (IPV); moral injury; and health services utilization in the 6 months preceding enrollment. Detailed descriptions of the assessment instruments used for each construct are provided in Table 1.

**Table 1 Tab1:** Primary and secondary outcome measures

Primary outcome measures		
Outcome measure	Measure description	Time frame
Beck's Scale for Suicidal Ideation (BSSI)	Suicidal ideation severity will be measured using the Urdu validated BSSI [34, 35]. The BSSI is a 19-item self-report instrument that assesses the intensity of suicidal thoughts, attitudes, and behaviors over the past 2 weeks. Each item is rated on a 3-point scale (0–2), with total scores ranging from 0 to 38; higher scores indicate greater severity of suicidal ideation	baseline and 6 months post-enrollment
Suicidal behaviors measured by Columbia Suicide Severity Rating Scale (C-SSRS)	Suicidal behaviors and attempts will be assessed using the C-SSRS [36]. The C-SSRS captures self-reported suicide attempts, aborted attempts, and interrupted attempts using dichotomous (yes/no) items. Any endorsement of these behaviors will be coded as a positive suicidal behavior outcome	baseline and 6 months post-enrollment
Secondary outcome measures		
Outcome measure	Measure description	Time frame
Patient Health Questionnaire—9 item (PHQ-9)	Depressive symptoms will be measured using the Urdu validated PHQ-9 [37], a 9-item self-report instrument assessing the frequency of depressive symptoms over the past 2 weeks. Items are rated on a 4-point scale ranging from 0 (not at all) to 3 (nearly every day), with total scores ranging from 0 to 27; higher scores indicate greater severity of depressive symptoms	Baseline, 3 and 6 months post-enrollment
Generalized Anxiety Disorder—7 item (GAD-7)	Anxiety will be measured using the Urdu validated GAD-7 [38], a 7-item self-report instrument. Items are scored on a 4-point scale from 0 (not at all) to 3 (nearly every day), with total scores ranging 0–21: higher scores indicate greater severity of anxiety symptoms	Baseline, 3 and 6 months post-enrollment
Multidimensional Scale of Perceived Social Support (MSPSS)	Social support will be measured using the Urdu-validated 12-item Multidimensional Scale of Perceived Social Support [39]. The MSPSS assesses perceived social support from three sources: family, friends, and significant others. Respondents rate each item on a 6-point Likert scale (0 = strongly disagree to 5 = strongly agree), with higher scores indicating greater perceived support	Baseline, 3 and 6 months post-enrollment
Maternal Suicide Risk Inventory (MSRI)	We developed this measure from formative interviews with 20 women with a history of suicidal behavior or clinical practice with suicidal women and 3 focus group discussions with Pakistani clinicians to identify inductively defined mechanisms of suicidality. The items will assess cognitive and emotional characteristics hypothesized to lie on the pathway to suicidality (e.g., loneliness, abandonment, helplessness, hopelessness, perceived burdensomeness, anger, and patience). Items are rated on a 3-point Likert scale and summed to yield total scores ranging from 16 to 48, with higher scores indicating greater suicide-related risk cognitions	Baseline, 3 and 6 months post-enrollment

### Follow-up assessments

All participants will be followed up at 3- and 6-months post-recruitment by trained research staff blinded to allocation status of the participants. Follow-up assessments will reassess suicidal ideation, depression, anxiety, perceived social support, suicide-related cognitions, intimate partner violence, moral injury, and health services utilization since the previous assessment. A subsample of purposively selected trial participants will be approached at 1 month and/or 6-months post-enrollment to qualitatively elicit experiences related to their suicidality, the trial, and the health system.

## Intervention groups

### EUC arm

Participants allocated to the control arm will receive EUC. Under this condition, LHWs will link women identified as at risk of suicide to their primary care facility-based MO. The MOs will be trained on the WHO mhGAP suicide prevention and risk assessment module [16]. In cases of imminent or lower-risk suicidality, LHWs will ensure participant’s immediate safety and facilitate a visit to the MO or higher-level specialty care as appropriate. In addition, all participants and healthcare workers will be provided with a nationally available suicide crisis hotline number supported by Taskeen, a Pakistani mental health organization.

### KPZ intervention arm

Participants allocated to the intervention arm will receive a total of 12 sessions delivered by a trained and supervised lay peer mother. KPZ comprises co-designed, brief suicide prevention interventions, including a decolonized approach to crisis and safety planning [31, 32], followed by structured follow-up sessions. These sessions explicitly target mechanisms identified in the grounded theory of maternal suicidality, including strengthening social connectedness, fostering *sabr* (patience), negotiating family and interpersonal stressors, and supporting the implementation of individualized coping and help-seeking strategies.

The decolonized safety planning component adapts conventional safety planning to enhance cultural relevance by reconstructing key domains to reflect mothers’ lived realities, employing a storytelling-based delivery approach, and incorporating visual illustrations created by Pakistani artists to convey the purpose and meaning of each step. Peer mothers will be trained in basic psychosocial support and in delivering all session content with fidelity.

All participants in the intervention arm will receive a KPZ booklet that accompanies each session. The booklet centers on the evolving story of a fictional character, Shagufta, whose experiences reflect common maternal stressors in the study context, allowing participants to relate their own life circumstances to the narrative. The booklet is primarily image-based rather than text-based to ensure accessibility for participants with limited literacy.

The 12 sessions will be delivered over a 6-month period. The first five sessions will occur within the first month, sessions 6 through 9 will be conducted biweekly, and sessions 10 through 12 will be conducted monthly. LHWs supporting participants in the intervention arm will follow the same safety monitoring procedures and referral pathways to MOs and higher-level care as outlined for the EUC arm.

## Intervention discontinuation and participant discontinuation criteria intervention will be discontinued if trial participants develop psychosis or another severe mental disorder.

### Loss to follow-up

Any participant who cannot be followed up at the designated time points (i.e., 3 and 6 months postnatal) will be considered lost to follow up and not contactable by the research team. Those who wish to withdraw consent from further intervention sessions; it will be recorded, and they will be asked if they wish to be followed-up or not, which will also be recorded. In case of consent withdrawal at any follow up, data collected up to that point of withdrawal will be included in the analyses.

